## 4.5 Safety Evaluation

The safety analysis will summarize drug exposure (including duration and dose) and adverse events (AEs) based on the safety analysis set population. The investigator is responsible for monitoring the safety of all subjects enrolled in this study, documenting any AEs, including: Serious adverse events (SAEs), Treatment-emergent adverse events (TEAEs) of Grade ≥3, TEAEs leading to treatment discontinuation or dose interruption/reduction/delay.

# 5. Sample Size

Both arms are expected to enroll 6-9 subjects each, with a total planned enrollment of 12-18 subjects.

# 6. Eligibility Criteria

## 6.1 Inclusion Criteria

Subjects can participate in the study only if all the following criteria are met:

(1) Patients with cTa-cT1N0M0 non-muscle invasive bladder cancer (NMIBC);

(2) Disease recurrence following intravesical anthracycline-based chemotherapy;

(3) Recurrent tumors confirmed as cTa-cT1N0M0 bladder urothelial carcinoma;

(4) No prior systemic chemotherapy exposure;

(5) Measurable lesions per Response Evaluation Criteria in Solid Tumors (RECIST);

(6) Eastern Cooperative Oncology Group (ECOG) performance status 0-1.

## 6.2 Exclusion Criteria

Subjects who meet any of the following criteria are not eligible to enter the study:

(1) Age <18 years;

(2) Subjects with severe cardiac, cerebral, hepatic, or renal dysfunction;

(3) Subjects with severe malnutrition;

(4) Subjects with psychiatric disorders or those lacking insight/unable to provide accurate expression;

(5) Concurrent malignancies in other organs;

(6) Presence of systemic infectious diseases.

## 6.3 Discontinuation Criteria

Discontinuation of study treatment does not equate to study withdrawal. Participants who discontinue study treatment must continue to complete all remaining study visits as required by the protocol. Study treatment must be discontinued if a participant meets any of the following criteria:

(1) The study participant withdraws informed consent and refuses to continue receiving the investigational drug treatment;

(2) The investigator determines that the participant's clinical symptoms have worsened/performance status has deteriorated;

(3) Disease progression is confirmed per RECIST v1.1 criteria;

(4) Despite dose modification, the participant remains unable to tolerate adverse events, including any clinical AEs, laboratory abnormalities, or other medical conditions;

(5) The participant commits a major protocol violation or demonstrates non-compliance with medical instructions;

(6) Occurrence of pregnancy, loss to follow-up, or death of the participant;

(7) Other circumstances where the investigator deems it necessary to discontinue the investigational drug treatment.

## 6.4 Withdrawal Criteria

(1) Withdrawal of informed consent - Participant refuses further study participation and follow-up.

(2) Lost to follow-up

(3) Death of participant

(4) Study termination

(5) Other investigator-determined reasons for withdrawal

## 6.5 Termination Criteria

The study may be prematurely terminated or temporarily suspended based on the following criteria:

(1) Identification of unexpected, significant, or unacceptable risks to study participants;

(2) Discovery of critical protocol flaws during trial execution.

# 7. Recruitment Method

This study is an exploratory clinical trial, and participants should be enrolled consecutively based on their willingness to participate. For potential participants, the investigator should discuss the possibility of enrollment. If the participant agrees, the investigator must verify that they meet all eligibility criteria. Eligible participants must sign the Informed Consent Form (ICF).

# 8. Overview of drugs

**Irinotecan Hydrochloride Liposome Injection:**

Specification: 8ml: 37.66mg (as C₃₃H₃₈N₄O₆)

Manufacturer: Jiangsu Hengrui Pharmaceuticals Co., Ltd.

Dosage Form: Injection

Route of Administration: Intravenous infusion

# 9. Special Adverse Reaction Management

In the event of the following special circumstances, appropriate measures for the investigational drugs shall be implemented.

## 9.1 Infusion-related reactions

This section is based on the infusion reactions and allergic reactions described in CTCAE 5.0, with some differences. Relevant handling measures suggestions have also been formulated for reference. Please refer to the table below for details. If infusion reactions or allergic reactions occur, the time needs to be recorded at least to the minute precision.

Table 1. Treatment measures for infusion reactions and allergic reactions

| **Infusion reactions and allergic reactions** | **Treatment measure** | **Subsequent administration** |
| --- | --- | --- |
| The reaction was transient and mild. No need to interrupt the infusion;  No treatment required | Reduce the infusion rate by 50%;  Monitor the research participants every 15 minutes to prevent the deterioration of their condition; | Reduce the infusion rate |
| The treatment or infusion needs to be interrupted and appropriate symptomatic treatment (such as antihistamines, non-steroidal anti-inflammatory drugs, anesthetics, intravenous administration) should be carried out promptly; preventive medication for no more than 24 hours is required. | Stop the administration;  50mg of diphenhydramine hydrochloride is intravenously infused, 650mg of acetaminophen is taken orally, and oxygen therapy is provided;  After the symptoms are relieved, the administration is resumed at a 50% infusion rate;  Monitor the study participants every 15 minutes to prevent the deterioration of the condition; | Reduce the infusion rate;  Preventively administer 25-50mg of diphenhydramine hydrochloride, intravenously, 10mg of dexamethasone, intravenously, and 650mg of acetaminophen, orally before administration. |
| Symptomatic bronchospasm with or without urticaria; requires parenteral treatment;  allergic-related edema/hemolytic anaphylaxis; hypotension | Stop the medication and remove the infusion tube;  50mg of Diphenhydramine hydrochloride is infused intravenously, 10mg of Dexamethasone is also infused intravenously. If bronchospasm occurs, use bronchodilators. Other drugs or oxygen therapy can be used as needed. | Prohibition of subsequent dosing cycles; |
| Life-threatening; requires urgent treatment | Stop the medication and remove the infusion tube; Administer epinephrine. If bronchospasm occurs, administer bronchodilators or oxygen therapy;  Intravenously infuse 50mg of diphenhydramine hydrochloride and 10mg of dexamethasone; Consider hospital observation. | Prohibition of subsequent dosing cycles; |

## 9.2 Diarrhea

Diarrhea caused by irinotecan liposome injection usually consists of both early-onset and late-onset diarrhea. Cholinergic action can result in early-onset diarrhea (occurring during or shortly after administration of the drug). It may be accompanied by rhinitis, increased salivation, miosis, tearing, diaphoresis, flushing, bradycardia, and hyperperistalsis that can cause abdominal cramps. If cholinergic syndrome occurs, atropine 0.25 to 1mg (total dose ≤1mg/ day) is recommended for treatment. Study participants who had acute cholinergic symptoms during previous treatment could receive atropine prophylactically until the next dose, at the investigator's discretion.

late-onset diarrhea (usually occurring after 24 hours after administration of irinotecan liposome injection, beginning with the first loose stool) may be of long duration and may result in dehydration, electrolyte disturbances, or infection, even fatal.

Once late-onset diarrhea occurs, it is recommended to give imodil treatment in time. Study participants were instructed to have imodium available and to start treatment if they had irregular or loose stools or more frequent bowel movements than previously reported. The imodil regimen was administered with an initial dose of 4mg, followed by 2mg every 2 hours until 12 hours after the study participants had stopped having diarrhea. In the evening, study participants could take Imodium 4mg every 4 hours. Continuous use of the above doses of imodil for more than 48 hours is not recommended because of the risk of paralytic ileus, nor is it recommended for less than 12 hours. Prophylactic administration of imodil is not recommended.

When diarrhea causes electrolyte disturbance and induces QTc interval prolongation, electrolyte supplementation is needed in time. When the underlying abnormality is recovered and the electrocardiogram is abnormal, the treatment can be continued with intensive monitoring, and the dose can be carefully adjusted.

If diarrhoea is present, it needs to be recorded at least to the hour.

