## 4.2 Dose Escalation Regimen

The dose-escalation scheme is designed based on a comprehensive evaluation of non-clinical in vitro pharmacodynamic data, existing clinical efficacy evidence and Safety profiles.

Arm A: Participants in this arm will complete the neoadjuvant therapy with irinotecan liposome (intravenous injection, once every two weeks for 1 month, dose increasing regimen: 37.6 mg/m2 and 56.5mg/m2) and epirubicin (intravesical instillation, once a week for 1 month, 50 mg).

Arm B: In the induction phase, the first three participants received a reduced dose of irinotecan liposomes (37.6 mg/m2, once every two weeks) in combination with standard intravesical EPI chemotherapy (50 mg, once a week) during the first cycle. If the combination was well tolerated, the irinotecan liposome dose was escalated to the full dose (56.5 mg/m2, once every two weeks) in the second cycle. The remaining three participants received the full dose of irinotecan liposomes (56.5 mg/m2, once every two weeks) along with standard EPI (50 mg, once a week) in both treatment cycles. Epirubicin was given at a fixed dose of 50 mg q1w for 4 cycles. In the maintenance phase, Epirubicin 50 mg q1m was intravesical instillation for a total of six cycles.

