## 4.3 Dose Escalation Principles

(1) Following the "3+3 principle", that is, three subjects were enrolled in each group, and the safety and tolerability of the first cycle were observed after administration. If no DLTS occurred, the trial proceeded to the next dose level according to the established dose-escalation protocol. If one DLT occurred, three more subjects were added at that dose level. When no new DLT occurred, the trial was continued at the next dose level. If ≥ 2 DLTS occurred, the dose level preceding that dose level was defined as MTD.

(2) The subjects with DLT were treated by the investigators according to the clinical diagnosis and treatment standards, and the dose could be delayed for no more than 2 weeks, the original dose could be maintained, or the dose level could be lowered to continue the next cycle. If no DLT occurred in the three patients enrolled in the first dose group during the observation period, the subsequent treatment was escalated to the second dose level.

(3) If more than one patient experienced DLT at the prespecified lowest dose, the lower dose was explored by the investigator.

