## 4.4 Treatment Period Follow-up

Arm A: routine blood test, liver and kidney function, coagulation function and adverse reactions were followed up every cycle after the first cycle of Irinotecan liposomal treatment. Pelvic and abdominal enhanced MRI and cystoscopy were performed after the second cycle of irinotecan liposomal treatment. The patients who achieved CR and PR were treated with TURBT combined with intravesical therapy after judged by two senior urologists. Patients with SD or PD received subsequent therapy at the investigator's discretion.

Arm B: Routine blood test, liver and kidney function, coagulation function and adverse reactions were followed up every cycle after the first cycle of Irinotecan liposomal treatment. Pelvic and abdominal enhanced MRI and cystoscopy were performed after combination treatment.

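### Protocol section 9.2 lets treatment continue after QTc prolongation when the electrocardiogram is 'abnormal'; this is most likely a slip for 'normal', and nothing elsewhere in the protocol corrects it

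*Protocol*

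**What the plan says.** The last part of Protocol section 9.2 deals with a chain of events: diarrhoea, then electrolyte disturbance, then QTc prolongation. It first sets the trigger and the immediate action: "When diarrhea causes electrolyte disturbance and induces QTc interval prolongation, electrolyte supplementation is needed in time". It then gives the rule for going on: "When the underlying abnormality is recovered and the electrocardiogram is abnormal, the treatment can be continued with intensive monitoring", and adds "and the dose can be carefully adjusted".

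Two more general rules could also bear on such a participant.

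- Section 4.3(2) applies if the event counts as a DLT. The participant is treated according to clinical standards, and options for the next cycle are listed: "the dose could be delayed for no more than 2 weeks, the original dose could be maintained, or the dose level could be lowered".
- Section 6.3 lists grounds for stopping treatment. The relevant ones are item 2 (clinical worsening or declining performance status), item 4 ("Despite dose modification, the participant remains unable to tolerate adverse events, including any clinical AEs, laboratory abnormalities, or other medical conditions") and item 7 ("Other circumstances where the investigator deems it necessary to discontinue the investigational drug treatment").

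**The concern.** The rule in 9.2 joins two conditions with 'and'. The first is that the cause has resolved. One expects the second to be that its effect on the heart has resolved too, but the text asks for an abnormal electrocardiogram.

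A site that follows the sentence as printed may give further study treatment while the tracing is still abnormal, in a participant who has just had QTc prolongation. Section 9.2 itself recognises that late-onset diarrhoea can disturb electrolytes and can be fatal, and safety is the trial's main purpose. What is at stake is participant safety. No estimate or test is affected.

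**Working it through.** The plan states no figure on this point, so there is nothing to reproduce. The check sets the texts side by side.

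**Step 1: what the printed rule permits.** Take the two conditions, cause recovered (yes or no) and electrocardiogram (normal or abnormal), and read the sentence literally.

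| Cause recovered | Electrocardiogram | 9.2 as printed | 9.2 with 'normal' |
| --- | --- | --- | --- |
| Yes | Normal | Not addressed | May continue |
| Yes | Abnormal | May continue | Not permitted by this rule |
| No | Normal | Not permitted by this rule | Not permitted by this rule |
| No | Abnormal | Not permitted by this rule | Not permitted by this rule |

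The printed rule is silent on the participant who has fully recovered, the first case a continuation rule should cover. It gives permission in the case that calls for caution. Replacing one word puts both rows right, which is why a slip is the likelier explanation. Table 1 in section 9.1 follows the same logic of recovery first: after an interrupted infusion, administration resumes once symptoms have eased.

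**Step 2: whether another section supplies the missing condition.** In the protocol text at hand, 'QTc' and 'electrocardiogram' each occur once, both in this part of 9.2.

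- Section 4.3(2) applies only after a DLT. It lists delay, same dose or lower dose as options and names no ECG or QTc criterion.
- Section 6.3, items 2, 4 and 7, rests on judgement or tolerability and names no ECG or QTc criterion.
- Sections 13.2 and 14.1.2 grade adverse events by CTCAE 5.0, but no grade is tied to holding or resuming treatment for QTc.

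Section 9.2 is therefore the only QTc-specific continuation rule, and nothing else overrides its wording.

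**Step 3: whether the alternative reading makes the sentence sound.** Suppose the intention is to continue despite a residual ECG change. The sentence would then allow dosing during unresolved QTc prolongation with no upper limit: it gives no QTc value, no change from baseline and no grade. On this reading too, the sentence needs rewriting.

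**Step 4: how many doses the rule could touch.** Irinotecan liposome is given "intravenous injection, once every two weeks for 1 month", which makes two doses. This fits the response assessment in section 4.4: "Pelvic and abdominal enhanced MRI and cystoscopy were performed after the second cycle of irinotecan liposomal treatment". After the first dose, 2 − 1 = 1 planned irinotecan dose remains. But 9.2 speaks of the treatment in general, section 9 opens by referring to the investigational drugs, and section 3.2 counts epirubicin among them. Weekly epirubicin may therefore also be covered. The protocol gives no frequency for the chain of events, so no number of affected doses can be derived.

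**The case against.** The strongest reply is that the slip is inferred. The sentence can be read as permission to continue despite a residual change once electrolytes are corrected, and intensive monitoring with careful dosing suits a tracing that is still abnormal. This stands as far as it goes: the intention cannot be settled from the page. It does not rescue the rule, because that reading leaves QTc without any limit.

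A second reply is that the rule is permissive and hedged. It says treatment can continue, it requires the cause to have recovered, and investigators may stop under 6.3 or manage a DLT under 4.3(2). All of this is true, and it limits the harm. A reader might infer that participants are left unprotected, and the documents do not support that. They show only that none of these controls corrects the ECG condition.

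A third reply is that a missing QTc cut-off is an omission, not an error. This is accepted. A reader might treat the absent threshold as a second fault, but if the electrocardiogram must be normal, no separate number is needed. A limit is required only if dosing on a residual change is intended.

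**Conclusion.** The point holds as a wording error in a safety instruction and should be fixed. As printed, section 9.2 permits continued dosing on an abnormal electrocardiogram after QTc prolongation, and no other section in the text states a condition that corrects it. That 'abnormal' stands for 'normal' is the most likely explanation, though not proven. The need to reword does not depend on it.

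The size is one sentence, applying only after diarrhoea, electrolyte disturbance and QTc prolongation in turn. A reader might multiply one remaining irinotecan dose by the 12 to 18 planned participants and call 12 to 18 re-doses a ceiling. The documents do not support that figure as a bound, because weekly epirubicin may also fall under the rule. It would also assume that every participant has the event after the first dose. The number of affected doses cannot be estimated. Endpoints, sample size and analysis are unaffected.

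**What to change.** Reword the sentence in 9.2 along these lines: treatment may be continued, with intensive monitoring and careful dose adjustment, only when the electrolyte disturbance has recovered and the electrocardiogram is normal, with QTc no longer prolonged. If continuing on a residual ECG change is intended, say so and state the QTc limit above which dosing must wait.

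A return to baseline should not be offered as the criterion without further change. The visit lists in sections 12.1 to 12.4 and 12.6 name no ECG, and the flowchart that the protocol cites is not in the text at hand, so no baseline tracing can be assumed.

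The cost is small: one sentence, and a repeat ECG before re-dosing in a participant already found to have QTc prolongation. The existing sentence already presupposes that tracing, since it makes the state of the electrocardiogram a condition.

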# 10. Concomitant Medications

All concomitant medications must be recorded in the Case Report Form (CRF), and the concomitant medications/treatments should be recorded from 28 days before the first dose to 30 days after the last dose. If a new antineoplastic therapy was initiated within 30 days after the last dose of the study drug, only concomitant medications/treatments for adverse events related to the study drug were recorded. After 30 days of the last dose, only concomitant medications/treatments used for follow-up for adverse events were recorded.

## 10.1 Prohibited Medications During the Study

The following systemic anti-tumor therapies are strictly prohibited during the study period, including but not limited to chemotherapy and immunotherapy not specified in the protocol, targeted therapy, modern traditional Chinese medicine preparations approved by the National Medical Products Administration (NMPA) for anti-tumor therapy, and immunomodulatory agents with adjuvant anti-tumor effects (such as thymosin, lentin, interleukin-12, etc.). These drugs may interact with Irinotecan and affect the plasma concentration of irinotecan.

## 10.2 Medications Requiring Cautious Use During the Study

Strong inducers/inhibitors of CYP3A4 and CYP2C8 or strong inhibitors of UGT1A1 should be used with caution during treatment. The above drugs may interact with irinotecan and should be used with caution. When combined with other drugs, it is recommended to choose alternative drugs that have no inhibition or induction of CYP3A4 and CYP2C8 enzymes. If they must be used at the same time with CYP3A4 and CYP2C8 enzyme inducers or inhibitors, it is necessary to consider whether to adjust the dose combined with clinical observation.

## 10.3 Supportive Care

Investigators should provide study participants with optimal supportive care when adverse events occur. The use of palliative and supportive care for disease-related symptoms will depend on the judgment of the investigator and relevant guidelines (e.g., the American Society of Clinical Oncology (ASCO) guidelines).

## 10.4 Nausea and vomiting treatment

Primary prevention of nausea and vomiting was permitted. The choice of prophylactic agent was left to the discretion of the investigator. The use of prophylaxis was approved if it was not included in the chapter on concomitant medications and there were no known or predictable drug interactions during treatment.

# 11. Administration, distribution and recycling of drugs

Personnel were responsible for the administration, distribution, and recycling of the study drugs, and investigators were required to ensure that all the study drugs were used only for the study participants who were enrolled in the study and that the doses and administration were in accordance with the study protocol. The remainder of the study drug was returned to the sponsor. The remaining liquid medicine was directly destroyed according to the standard of medical waste. Study drugs were stored according to the instructions.

Study monitors were responsible for monitoring the supply, use, storage, and management of the surplus of study drugs.

# 12. Study Procedure

Before study initiation, all participants must read and sign the current Ethics Committee approved ICF. All examinations and trial procedures shall be conducted according to the schedule specified in the study flowchart, irrespective of the duration of any treatment discontinuation. However, adjustments within the predefined visit windows are permitted due to holidays, festivals, or other administrative reasons. All examinations are recommended procedures and may be modified based on actual clinical circumstances.

## 12.1 Screening period

First, confirm whether the study participant has signed the ICF. Except for pre-existing tumor imaging examinations and pathological diagnoses conducted within the specified timeframe before initial treatment, written informed consent must be obtained prior to performing any clinical study procedures.

The screening period begins upon signing the ICF and ends either at randomization or upon screening failure. Study participants who withdraw from the study after signing the ICF but before randomization will be considered "screening failures." This study allows previously screened participants who failed screening to re-enter the screening process, provided they re-sign the ICF and are assigned a new participant identification number.

The interval between signing the ICF and the first treatment must not exceed 21 days. Final eligibility for study participation will be assessed within the designated timeframes outlined in the visit schedule.

During the screening period (Days -28 to -1), the following study procedures must be completed to confirm participant eligibility:

- Signing of ICF
- Verification of inclusion/exclusion criteria
- Documentation of demographic data, medical history, and prior medications
- Recording of vital signs, height, and weight
- Physical examination
- ECOG PS assessment
- Complete blood count/blood chemistry (within 7 days prior to first dose)
- Coagulation function tests (within 7 days prior to first dose)
- Myocardial enzymes
- Pregnancy test (within 72 hours prior to first dose)
- Adverse event assessment
- Concomitant medications and treatments
- Tumor imaging evaluations: Pelvic MRI (plain + contrast-enhanced);

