## 14.4 Abnormal liver function

If AST and/or ALT levels are abnormal and the TBIL level is abnormally increased, and the following conditions are met and there are no other reasons for the abnormality, the SAE reporting procedure should be followed.

| conditions | criteria |
| --- | --- |
| (1) Abnormal ALT or AST | Normal baseline: ALT or AST > 3× upper limit of normal (ULN) during treatment;  Abnormal baseline: ALT or AST > 2× baseline level and value > 3× ULN during treatment; Or > 8× ULN; |
| (2) Abnormal TBIL | Normal baseline: TBIL > 2×ULN during treatment;  Abnormal baseline: TBIL increased > 1×ULN or its value > 3×ULN during treatment; |
| (3) No hemolysis and alkaline phosphatase < 2×ULN (or information not available) | |

Participants who had an abnormal AST and/or ALT level combined with an abnormally elevated total bilirubin level during the safety follow-up period were advised to return to the study center for evaluation and confirmation as soon as the abnormal result was known, preferably within 48 hours.

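### The screening pregnancy test, blood count and coagulation tests are required to confirm eligibility, but no entry criterion uses pregnancy status, marrow function or coagulation

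*Protocol*

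**What the plan says.** Section 12.1 introduces its screening list by stating that "the following study procedures must be completed to confirm participant eligibility". The list includes:

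- "Pregnancy test (within 72 hours prior to first dose"
- "Complete blood count/blood chemistry (within 7 days prior to first dose"
- "Coagulation function tests (within 7 days prior to first dose"

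It gives no result that would bar entry.

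The inclusion criteria (Section 6.1) cover tumour stage, recurrence after intravesical anthracycline, urothelial histology, no prior systemic chemotherapy, measurable disease and performance status. The exclusion criteria (Section 6.2) cover age, organ dysfunction, malnutrition, psychiatric disorder, other malignancy and systemic infection. The only organ-function item is "Subjects with severe cardiac, cerebral, hepatic, or renal dysfunction", with no values attached. The synopsis carries the same two lists.

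Pregnancy reappears in Section 6.3, where item 6 makes "Occurrence of pregnancy, loss to follow-up, or death of the participant" a reason for mandatory discontinuation of study treatment. It also appears in Section 14.7, which treats certain pregnancy outcomes as serious adverse events.

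**The concern.** A test done to confirm eligibility should have a criterion that its result can fail. For pregnancy status, marrow function and coagulation there is none. Section 7 asks the investigator to verify that every eligibility criterion is met, and a positive pregnancy test or a very low neutrophil or platelet count would not breach any of them.

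The first thing at stake is participant safety. The protocol treats pregnancy as incompatible with study treatment once treatment is under way, and tests for it within three days of the first dose, yet attaches no entry consequence to the answer.

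The second is the primary endpoint, the incidence and frequency of DLT. Cohorts are of three, and one participant's outcome can change the path of the trial. Someone who enters with a low count may need only a small further fall to cross a toxicity grade.

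**Working it through.** **Step 1. Match screening tests to criteria.**

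| Screening item (12.1) | Criterion it can inform (6.1, 6.2) | Later rule |
| --- | --- | --- |
| Pregnancy test | None | 6.3(6): treatment must stop |
| Blood count, as marrow function | None | None at entry |
| Coagulation tests | None names coagulation | None at entry |
| Blood chemistry, myocardial enzymes | 6.2(2), organ dysfunction, no values | n/a |
| ECOG assessment | 6.1(6) | n/a |

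The first three rows have no matching criterion.

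**Step 2. Look for a back-stop.** The discontinuation list (6.3, item 7) and the withdrawal list (6.4, item 5) each end with an item left to the investigator's judgement. Section 6.2 ends at systemic infection and has no such item.

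**Step 3. Can a baseline abnormality reach the DLT count?** Section 14.1.1 records a pre-existing condition, including a laboratory abnormality, as an adverse event only if it worsens after treatment starts. An unchanged low count is therefore not an adverse event. A low count that worsens and crosses a grade is one. Whether it would be a DLT cannot be determined, because the protocol gives no toxicity, grade or window that defines a DLT.

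**Step 4. Size, if it did count.** The protocol gives no DLT probabilities, so those below are assumptions. The rule is that of Section 4.3(1): escalate after no DLT in three, or after one DLT in three followed by none in three more. Participants are taken as independent. Let *p* be the background DLT risk and *q* the risk of one cytopenic participant among the first three; the three added participants have risk *p*.

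- All at *p*: P(escalate) = (1−p)³ + 3p(1−p)² × (1−p)³. With p = 0.10: 0.729 + 0.243 × 0.729 = 0.906.
- One at *q*: P(0 of 3) = (1−q)(1−p)²; P(1 of 3) = q(1−p)² + (1−q) × 2p(1−p); P(escalate) = P(0 of 3) + P(1 of 3) × (1−p)³.
  - q = 0.30: 0.567 + 0.369 × 0.729 = 0.836
  - q = 0.50: 0.405 + 0.495 × 0.729 = 0.766
  - q = 0.70: 0.243 + 0.621 × 0.729 = 0.696

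The same calculation at other background risks:

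| Background p | No such participant | q = 0.30 | q = 0.50 | q = 0.70 |
| --- | --- | --- | --- | --- |
| 0.05 | 0.973 | 0.921 | 0.879 | 0.837 |
| 0.10 | 0.906 | 0.836 | 0.766 | 0.696 |
| 0.15 | 0.814 | 0.748 | 0.661 | 0.574 |
| 0.20 | 0.709 | 0.661 | 0.566 | 0.471 |

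**The case against.** The strongest reply is that no investigator would dose a pregnant or severely cytopenic patient, that nothing obliges the investigator to enrol everyone who meets the criteria, and that 6.3(6) shows pregnancy was considered. This is fair about likely conduct. But the refusal would rest on judgement outside the written criteria, and 6.3(6) acts on treatment, not on entry. The mismatch between Sections 6.2, 6.3 and 12.1 remains.

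It can also be said that not every item in the 12.1 list is meant to map to a criterion, since the list includes adverse event assessment and concomitant medication. That is true, but a pregnancy test timed to 72 hours before the first dose has little purpose at that point other than deciding entry.

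Several stronger readings are tempting, and the documents do not support them:

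- A reader might infer that the screening blood tests in general serve no criterion. Chemistry and myocardial enzymes can inform exclusion 2. Protein and albumin could bear on severe malnutrition, and white-cell counts on systemic infection. The gap is confined to pregnancy status, marrow function and coagulation.
- A reader might infer that someone already at a high grade at baseline would be counted as a DLT. Section 14.1.1 rules this out unless the value worsens.
- A reader might take Section 14.4, with its line "Abnormal baseline: TBIL increased > 1×ULN or its value > 3×ULN during treatment", as a sign that unsuitable participants are expected. It is a reporting rule adjusted for baseline. It is consistent with an exclusion that bars only severe hepatic dysfunction.
- A reader might link pregnancy to distortion of the DLT rate. Nothing in the protocol makes that link.
- A reader might measure the effect by the chance of a first cohort free of DLT, which at p = 0.10 and q = 0.50 falls by 0.729 − 0.405 = 0.324. One DLT only adds three participants and does not stop escalation. Under the full rule the fall is 0.906 − 0.766 = 0.140.

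**Conclusion.** The point holds as an inconsistency between the screening list, the eligibility criteria and the discontinuation rule. Followed as written, the protocol admits a participant with a positive screening pregnancy test and one with marked baseline cytopenia. That conclusion rests on the text alone and needs no assumption. It concerns participant safety first.

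The effect on the primary endpoint is secondary and conditional. It requires that a worsening cytopenia counts as a DLT, which the protocol neither states nor excludes, and that such a participant falls in the first three. On the assumed risks (10% background, 30% to 70% for that participant) the chance of escalating drops by 0.07 to 0.21, from 0.906 to between 0.836 and 0.696. These figures show how sensitive a cohort of three is. They do not forecast this trial.

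**What to change.** Reconcile Sections 6.1, 6.2, 6.3(6) and 12.1, and the matching synopsis rows, so that the result of the screening pregnancy test decides entry in a way consistent with 6.3(6). Add one eligibility criterion that uses the blood count and coagulation results already collected within 7 days of the first dose, with limits set by the investigator. No limit is proposed here. The limits cannot be tied to a DLT grade until the protocol defines DLT, which is a separate gap that this change does not close.

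The cost is two added criteria, using tests already scheduled, and a protocol amendment that goes back to the Ethics Committee under Section 17. There may be a few more screening failures; the documents give no basis for estimating how many.
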